### Outcomes

#### Primary outcomes

Participants diagnosed with moderate-to-severe OSA, defined as an AHI reading of
15–30 (moderate) or >30 (severe) episodes per hour.The AcuPebble report for those in the intervention group and the GP notes review
for those in the usual care group will be reviewed 6 months after
randomisation to identify any diagnoses of moderate-to-severe OSA since
randomisation.

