### Intervention arm

Participants randomised to the intervention arm will receive the overnight sleep testing
AcuPebble device from Acurable by post. Simple participant instructions, including how and
where the device is placed, are given via a dedicated mobile app (phone supplied with app
if required). Should the test fail, a new test code will be sent to the participant
enabling a repeat test before the device is returned in prepaid addressed envelope. When
the test is complete, the test data are automatically uploaded directly to
Acurable’s secure platform, allowing them to provide the diagnosis, as validated in
their study, using their algorithm.

The sleep study platform will include the Epworth Sleepiness Scale (ESS) and an optional
brief questionnaire to assess acceptability of the intervention. The number of
completed/valid tests, number of failed tests and returned devices will be an indication
of feasibility. Participants are expected to perform the sleep testing within a week of
receipt of the AcuPebble device. Participants will be followed up remotely 6 months from
the date of randomisation. Data will be collected both from participants and medical notes
review.

The results of the sleep studies will be reviewed by our sleep consultant to confirm any
diagnoses of OSA. He will notify the participant’s GP of the results and advise
whether the patient needs to be referred to the sleep clinic for treatment or further
investigation.

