### Follow-up

Participants will be followed up at 6 months from point of randomisation. All
participants will be asked to complete repeat measures of the EQ-5D-5L with VAS, CSRI and
a short OSA questionnaire. Two reminders will be sent, but any participants who have not
returned their completed questionnaires within 1 month of the date of posting will
be considered non-responders and their questionnaires considered missing.

The GP notes of all participants in the usual care group will be reviewed to identify any
diagnoses of OSA since randomisation (primary outcome) and for those with a positive
diagnosis, time to diagnosis, time to commencement of treatment and type of treatment
prescribed.

For those in the intervention group *diagnosed with OSA* since
randomisation, their GP notes will be reviewed to determine time to commencement of
treatment and type of treatment prescribed. The GP notes of those who were referred for
further investigation will also be reviewed to confirm whether a subsequent diagnosis of
moderate-to-severe OSA was made, and if so, details of any treatment started.

Reviewing the GP notes of those in the intervention group who tested negative for OSA and
needed no further follow-up is considered unnecessary, as no further information is
required for this trial, and hence there is no justification for accessing
participants’ medical information. A variety of means of communication will be used
to both raise awareness in the practice and to gain a response or to send invitations.
Texts and emails will also be used where appropriate.

Any subsequent post-trial visits and treatment by the GP or sleep clinic are not part of
the research and represent a return to the usual care pathway after diagnosis.

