### Sample size determination

The detection rate of new cases of moderate-to-severe OSA using usual care is estimated
at <5% per year. Given the previously observed rates of hypertension (39%), obesity
(34%) and diabetes mellitus (15%) in individuals with OSA, we would expect that the
targeted case finding intervention would yield a detection rate of 10% or more in the
high-risk groups. The study has been powered (90%) at 5% two-sided significance level to
detect a 5% difference in rate of new cases of moderate-to-severe OSA between intervention
and usual care. The study will require 606 participants in each arm. To allow for 15%
attrition and lost to follow-up, it is anticipated that 713 in each arm need to be
recruited.

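### Usual-care diagnoses are read from GP notes at 6 months with no stated allowance for late filing, so some made inside the window can be missed, mainly in the control arm

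*Protocol article*

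**What the plan says.** The two arms take the primary outcome from different sources. For the intervention arm it is the AcuPebble report. For control, GP notes "for those in the usual care group will be reviewed" six months from randomisation, looking for moderate-to-severe OSA diagnosed since randomisation (Primary outcomes). The Follow-up section repeats the control source: "The GP notes of all participants in the usual care group will be reviewed to identify any" OSA diagnosis, with time to diagnosis and treatment details for those found positive. Secondary outcomes uses the same six-month review for times to testing, diagnosis and treatment.

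In the Intervention arm section, once a test is complete "the test data are automatically uploaded directly to" the manufacturer's platform. Testing is expected within a week of receiving the device, and a sleep consultant then confirms any diagnosis.

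Follow-up also sends some intervention participants to the GP record. Notes are read for treatment details in those diagnosed, and for a later moderate-to-severe diagnosis in those referred on. Notes of test-negatives needing no further follow-up are not read.

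For size, Sample size determination puts usual-care detection below 5% per year and expects that the "intervention would yield a detection rate of 10% or more in the" high-risk groups.

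**The concern.** The window opens at randomisation, and its only stated close is the notes review. A usual-care diagnosis is made in a hospital sleep service and has to be reported to the practice and filed before a notes reviewer can see it. If notes are read at six months and not looked at again, a diagnosis made in the preceding weeks may be real, inside the window and still invisible.

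The point covers only diagnoses already made but not yet filed. A referral still waiting for a test at six months is correctly a non-event, and a diagnosis made after six months is outside the window in either arm.

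The device report has little exposure to this delay. A true control event can thus be scored as a non-event by the timing of the review, with much less corresponding loss in the intervention arm. That pushes the detection difference towards the intervention. It also carries into the economic evaluation, which reports additional cases detected. Treatment starts come from GP notes in both arms, so late filing can lose some in each, and the article does not show which arm would lose more.

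**Working it through.** **The plan's own figure.** The design aims to "detect a 5% difference in rate of new cases of moderate-to-severe OSA between intervention" and control, and asks for 606 per arm. For 5% against 10%, two-sided 5% level and 90% power, the usual two-proportion formula gives 582 per arm without continuity correction and 621 with it. The stated 606 lies between them, and power at 606 is 91.2%. The attrition step is exact: 606 / 0.85 = 712.9, which matches the 15% allowance for "attrition and lost to follow-up, it is anticipated that 713 in each arm need to be" recruited. The sample size is therefore sound for its inputs and serves here only as a base.

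**Inputs for the lag.**
- Control detection over six months: below 5% per year, so about 5% / 2 = 2.5% at a constant rate (Sample size determination). The alternative reading, 5% at six months, is shown beside it.
- Intervention detection: 10% (same section).
- Evaluable participants per arm: 606.
- Lag L between diagnosis and its appearance in the GP record: not given. Assumed 2, 4 or 8 weeks.
- Timing of control diagnoses: assumed even over 26 weeks.

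**Formulas.** Share missed = L / 26. Diagnoses missed = 606 × rate × L / 26. Overstatement in percentage points = rate × L / 26.

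Expected control diagnoses are 606 × 0.025 = 15.2, or 606 × 0.05 = 30.3.

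| Lag (weeks) | Share missed | Missed at 2.5% | Overstatement at 2.5% | Missed at 5% | Overstatement at 5% |
|---|---|---|---|---|---|
| 2 | 7.7% | 1.2 | 0.2 points | 2.3 | 0.4 points |
| 4 | 15.4% | 2.3 | 0.4 points | 4.7 | 0.8 points |
| 8 | 30.8% | 4.7 | 0.8 points | 9.3 | 1.5 points |

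At 2.5% the expected difference is 10 − 2.5 = 7.5 points, and it would be observed as 7.7, 7.9 or 8.3. At 5% it is 5.0 points, observed as 5.4, 5.8 or 6.5.

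**Sensitivity to the even spread.** The Introduction reports that time to treatment in one local service was well over 4 months before the pandemic. If control diagnoses therefore fell only in the second 13 weeks, a 4-week lag would lose 4 / 13 = 31%, the same as the 8-week row.

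**Effect on the test.** With 606 per arm, 10% against 2.5% has power above 99.9% with or without the lag. The issue is the size of the estimate, not whether the trial detects a difference.

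**The case against.** The strongest reply is that the article fixes a time point, not a calendar day. It does not say that notes are read exactly at six months, and a condensed article may leave an extraction window to the full protocol. Some of its text fits later extraction: service use is to cover the whole six months after randomisation, follow-up questionnaires have up to a month to come back, and the trial ends with the last notes review. Times to test and diagnosis are already collected, so events can be dated independently of the review. This stands as a reason for caution. It does not remove the point, because the stated rule still ties the control outcome to a six-month review, with neither a separate closing date nor a second look.

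A reader might infer that the loss is confined to control, or that device results are immediate. The documents support neither. Intervention participants referred on also depend on GP notes, treatment starts are read from notes in both arms, and device results follow posting, testing, a possible repeat and consultant confirmation. Usual-pathway diagnoses in test-negative intervention participants are not looked for, which works in the opposite direction, but that is a separate matter and does not cure this one.

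The manual scoring described under Review of the evidence comes before diagnosis, so it is no evidence of a filing delay. Leading with 5% as the six-month control rate would also double the effect relative to the article's annual figure.

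**Conclusion.** The point holds in a limited form. As the article states the rule, diagnoses made inside the window but filed late can be missed, mainly in usual care, which gives a small bias towards the intervention. With 2.5% control detection over six months and lags of 2 to 8 weeks, it amounts to about 1 to 5 missed diagnoses per 606 and 0.2 to 0.8 percentage points on an expected 7.5. These figures double if 5% applies at six months. They rest on an assumed lag and an even spread of diagnoses, since the documents give neither.

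It would be tempting to conclude that the bias could produce the trial's result. The figures do not support that, and the conclusion is unlikely to reverse. The point is worth acting on because the correction is cheap and the bias runs mostly in one direction.

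**What to change.** Define the primary outcome as moderate-to-severe OSA with a test or specialist diagnosis dated within six months of randomisation, and use that date, not the date of GP coding. Then do one of two things:

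- extract the notes after a fixed lag chosen by the trial team; or
- keep the six-month review and query the record once more before database lock.

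Apply the same rule to every participant in either arm whose notes are reviewed, and date treatment starts in the same way.

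The cost is an amendment to the Follow-up and Outcomes sections. With a fixed lag, the last notes reviews, and so the end of the trial, move by that lag, which matters against a planned end in April 2025. Records already extracted need one extra query. No new participants or procedures are needed, and the six-month cut-off can still be applied because diagnosis times are already collected. If the full protocol already has such a rule, a sentence confirming it is enough.

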#### Secondary outcomes

Time to completion of testing from randomisation, time to diagnosis from
randomisation and time to treatment from randomisation for new pathway (intervention
group) versus usual care. For those diagnosed with moderate-to-severe OSA (as
detailed above for both the intervention and usual care groups) and OSAS, their
AcuPebble or GP notes will be reviewed 6 months after randomisation to
determine time to completion of testing, time to diagnosis, time to commencement of
treatment and type of treatment prescribed. For the usual care pathway, we will also
look at the individual components of the usual referral pathway, that is, time to
test from referral, time to diagnosis from referral, time to treatment from
referral. Date of referral is defined as date when the patient was referred.Detection of participants diagnosed with any OSA (mild, moderate, severe), defined
as an AHI reading of ≥5 to <15 (mild), ≥15 to
<30 (moderate) or ≥30 (severe) episodes per hour for new
(intervention) versus usual care pathway. This will be determined from the AcuPebble
report for those in the intervention group and the GP notes review for those in the
usual care group.Detection of participants diagnosed with OSAS, defined as those with OSA (mild,
moderate, severe (as above)) and with evidence of EDS (ESS score >11) for new
(intervention) versus usual care pathway. This will be determined from the AcuPebble
report for those in the intervention group and the GP notes review for those in the
usual care group.Health-related quality of life associated with new and current pathways. QALYs will
be calculated based on information collected from participants at baseline and
6 months using the EQ-5D-5L.Cost-effectiveness analysis comparing new and current pathways. All participants
will be sent follow-up questionnaires either by email or post (as detailed above);
these will include the EQ-5D-5L with VAS, CSRI and information about procedures
undertaken to diagnose or treat moderate-to-severe OSA since randomisation. Further
data on health service usage will be obtained from the participant notes review
undertaken at 6-month follow-up. This review will collect data on service usage
related to sleep issues in the 6 months prior to date of randomisation to
provide a baseline value and during the 6 months after randomisation to
provide follow-up data.Feasibility and acceptability of new sleep study testing to be tested against the
following criteria in the feasibility phase: (1) the number of GP practices
recruited and set up (four required for feasibility; No-Go criteria: only one
practice recruited); (2) to recruit 80 patients within 2 months of the first
patient recruited (No-Go: <50% recruited); (3) AcuPebble testing successfully
implemented; (4) at least 90% intervention completion (No-Go: <50%
completion). Participants using the AcuPebble also have the option to complete a
brief survey about their experience of using the AcuPebble on the AcuPebble app,
following the completion of their sleep study. These are standard questions
currently asked and analysed by Acurable for all AcuPebble users.

### Schedule of delivery of intervention and data collection

The trial events’ schedule and data assessments are summarised in table 1.

**Table 1 T1:** Trial schedule of events and data collection

	Before randomisation	Baseline+randomisation	Intervention group	6 months
	Remote	Face to face	Remote by Acurable	Remote
Identification of eligible patients (inclusion/exclusion criteria)	✓			
Invitation to participate in study	✓			
Written and witnessed informed consent		✓		
Collection of questionnaires (Clinical and Health Economics)		✓		✓
Randomisation		✓		
Delivery of AcuPebble			✓	
Analysis of OSA test and reporting outcome			✓	
Primary outcome				✓
Secondary outcomes				✓

OSAobstructive sleep apnoea

### Discontinuation/withdrawal of participants from study

If the participant wishes to withdraw from follow-up, we will use their data up to the
point that they discontinue from the trial. No participants will be replaced if they are
discontinued or withdraw. Participants will only be withdrawn from the intervention by the
research team should the intervention be deemed unsafe, or withdrawn from the trial if
participant subsequently found to be ineligible. Reasons for withdrawal will be captured
and recorded in the trial database.

### End of study

The end of the trial is the final data capture of the last participant’s GP notes
review.

### Adverse event management

The safety reporting window for the trial will be defined as the period between
randomisation and 6-month follow-up of each participant in the trial.

This trial will only collect adverse events (AEs) potentially related to the AcuPebble
device. Hence, participants will be encouraged to self-report any AEs and serious adverse
events in the 4 weeks following randomisation directly to the trial office and will
be reviewed and reported on as per the Good Clinical Practice (GCP).

### Data management

Details of the data management procedure are documented in a trial-specific data
management plan reviewed and signed by all applicable parties prior to the first
participant being enrolled. The data management will be run in accordance with the Primary
Care Clinical Trials Unit (PC-CTU) standard operating procedures (SOPs), which are fully
compliant with GCP. The trial will comply with the UK General Data Protection Regulation
(GDPR) and Data Protection Act 2018, which require data to be anonymised as soon as it is
practical to do so.

AcuPebble SA100 is a registered NHS device and data will be stored in the UK. The
AcuPebble data will be downloaded in .csv format from the AcuPebble SA100 web application,
and then uploaded to the clinical database that is managed and hosted by the University of
Oxford PC-CTU. Pseudonymised study data, only accessible by relevant members of the data
management team, are stored on regularly backed-up, VPN secure network drives in
accordance with the GDPR and participants’ consent.

### Data sharing plan

Due to the sensitive nature of the medical data collected for this trial (ie, individual
risk factors and disease diagnosis), the full data set will not be placed in a public
access repository but will be available, on request, from the lead author.

### Sample size determination

The detection rate of new cases of moderate-to-severe OSA using usual care is estimated
at <5% per year. Given the previously observed rates of hypertension (39%), obesity
(34%) and diabetes mellitus (15%) in individuals with OSA, we would expect that the
targeted case finding intervention would yield a detection rate of 10% or more in the
high-risk groups. The study has been powered (90%) at 5% two-sided significance level to
detect a 5% difference in rate of new cases of moderate-to-severe OSA between intervention
and usual care. The study will require 606 participants in each arm. To allow for 15%
attrition and lost to follow-up, it is anticipated that 713 in each arm need to be
recruited.

## Statistical methods

Feasibility outcomes will be assessed descriptively and reported to the data monitoring and
safety committee and trial steering committee.

The study results will be reported in accordance with the Consolidated Standards of
Reporting Trials 2010 reporting guidelines (www.consort-statement.org/downloads/consort-statements) and a statistical
analysis plan will be prepared before recruitment starts.

Baseline variables will be presented by randomised group descriptively. Trial results
presented as comparative summary statistics with 95% CIs. All tests will be done at a 5%
two-sided significance level.

The primary analysis will include all randomised participants, as defined by protocol
eligibility criteria, regardless of what intervention they actually received or compliance
of intervention. The primary analysis of the primary outcome (detection of
moderate-to-severe OSA) will be performed using a logistic generalised linear mixed effects
model, adjusting for minimisation factors (age, sex and ethnicity) as fixed effect and
general practices as random effect. A similar approach will be used for other secondary
binary outcomes. Time-to-event outcomes will be analysed using a Cox regression model with
similar adjustment as the primary analysis. Secondary analysis of time to starting treatment
will include the primary analysis population who were diagnosed with moderate-to-severe OSA
and individuals with evidence of EDS/OSAS. Participants not starting treatment will be
censored at last contact date.

Missing data will be reported and the missing data pattern will be explored. Additional
sensitivity analysis using imputation methods will be performed. Safety outcomes of the
intervention will be descriptive.

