### Review of the evidence

In OSA, complete closure (obstruction) of the airway during sleep stops airflow (apnoea),
whereas partial obstruction decreases airflow (hypopnoea) resulting in episodes of brief
awakening from sleep (arousals) to restore normal breathing.^16^ The number of apnoeas/hypopnoeas per hour of sleep
defines the apnoea-hypopnoea index (AHI) and gives an indication of disease severity.^17^ In 1993, the prevalence of OSA was 4% in
middle-aged men and 2% in middle-aged women (ages 30–60 years).^14^ In 2019, Benjafield *et
al* estimated that 425 million adults aged 30–69 have moderate-to-severe
sleep apnoea globally.^18^ In a study
published in 2021, using the Clinical Practice Research Datalink, which represents 8.5% of
primary care practices in the UK, the prevalence of OSA in obese patients was 8.4% in men
and 3.7% in women.^19^ Male sex, high body
mass index (BMI), hypertension and diabetes were the most common risk factors.^19^ The new NICE guidance recognises that OSA
is also highly prevalent in individuals with other conditions like polycystic ovary
syndrome, atrial fibrillation and hypothyroidism.^7^ Higher prevalence rates have been reported in some high-income
countries.^20 21^ OSA is associated
with both type 1 and type 2 diabetes^19 22 23^ and increased BMI,^19 24^ and is a frequent cause of resistant hypertension.^25^,^27^

Current NICE guidelines recommend that adults who are sleepy while driving or working
with machinery, are employed in hazardous occupations (eg, pilot, bus or lorry driver) or
show signs of respiratory or heart failure (with symptoms suggestive of OSA) should be
referred urgently to sleep centres.^28^
However, GPs may not always ask sleep-related questions, and information received may not
be followed up or acted on.^29^ Indeed,
20% of people with OSA had visited their GP on three or more occasions with symptoms and
no action was taken in 11%.^4^

The most common form of treatment is CPAP,^2^ although other treatments are used.^30^ Treating moderate-to-severe OSA can generate health benefits and
improve the quality of life of patients, especially those with OSAS who experience an
improvement in EDS, and a reduction in risk of RTAs.^31 32^ CPAP is also an effective management in patients with
resistant hypertension.^4^

In 2008, NICE appraised the use of CPAP compared with lifestyle management and dental
devices for the treatment of adults with moderate-to-severe OSA. It concluded that CPAP is

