### Eligibility

#### Inclusion criteria

Adults aged between 50 and 70 years with BMI≥30 kg/m^2^ as of GP
records in the last 3 years AND documented (a) diabetes (type 1 or 2) OR (b)
hypertension (office BP>145/90 mm Hg or on treatment) OR (c) both (hypertension
and diabetes).

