### Randomisation and blinding

Figure 2 shows the design of the study. Participants
will be randomised (1:1) to receive the intervention or usual care using a validated
web-based randomisation programme (sortition). Randomisation will be minimised with a
non-deterministic minimisation algorithm to ensure site, age (<60/≥60
years), sex (F/M) and ethnicity (White/Other) are balanced across the two groups.
Individual randomisation is appropriate because the risk of contamination is very low,
since the device is sent to participants directly and the assessment of the primary
outcome (diagnosis of moderate-to-severe OSA) will be automated (unbiased).

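### The primary model is valid, but it leaves out BMI and qualifying condition, two eligibility variables that could add a little precision at low cost

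*Protocol article*

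**What the plan says.** The Statistical methods section of the protocol article names a logistic generalised linear mixed effects model for detection of moderate-to-severe OSA. Its fixed effects are given as "model, adjusting for minimisation factors (age, sex and ethnicity) as fixed effect and", and the sentence continues with "general practices as random effect. A similar approach will be used for other secondary" binary outcomes. Randomisation and blinding gives the minimisation factors as site, age (under 60 v 60 and over), and then "years), sex (F/M) and ethnicity (White/Other) are balanced across the two groups". The model therefore contains all four minimisation factors, with site entering as the practice random effect.

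Review of the evidence, citing a UK primary care database study, says that male sex and high body "mass index (BMI), hypertension and diabetes were the most common risk factors". Of these four, only sex is in the model.

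Inclusion criteria begin "Adults aged between 50 and 70 years with BMI≥30" and require that BMI to come from GP records of the last 3 years, together with documented diabetes, hypertension or both. The Sample size determination section also relies on the rates of hypertension, obesity and diabetes among people with OSA to justify an expected detection rate of 10% or more.

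**The concern.** The protocol treats BMI, diabetes and hypertension as drivers of OSA risk when it selects patients and when it justifies the expected detection rate. It then neither balances these variables at allocation nor adjusts for them in the primary model. If they still predict detection among the enrolled patients, adjustment would recover some precision and remove the effect of chance imbalance between arms. The information must exist for every participant, because nobody is eligible without it. What is at stake is a modest amount of efficiency in the primary comparison, and in the other models that reuse this covariate set.

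**Working it through.** **1. The plan's own figure.** Inputs from Sample size determination: control rate 5% (stated as under 5% per year), intervention rate 10%, two-sided 5%, power 90%, 15% attrition.

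- Two-proportion formula, with mean rate 0.075: n = [1.960·√(2·0.075·0.925) + 1.282·√(0.05·0.95 + 0.10·0.90)]² / 0.05² = 582 per arm. With continuity correction it is 621. The stated 606 lies between the two.
- Uncorrected power at 606 per arm is 91.2%.
- Attrition: 606 / 0.85 = 712.9, so 713, as stated.

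The calculation does not rely on covariates, so nothing below alters it.

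**2. What the extra covariates might buy.** The protocol gives no association between BMI or qualifying condition and detection in this population, so these are assumed. Setup: 606 per arm, 5% v 10%, right-skewed BMI above 30 in SD units. The mix is 20% diabetes only, 50% hypertension only and 30% both. Odds ratios are 2 for sex and 1.2 for age, with 20% in the Other ethnicity group and no ethnicity effect. There is no practice effect. The planned fixed effects are compared with the same model plus BMI and two indicators for condition, over 3,000 simulated trials per scenario.

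| Assumed odds ratio (per SD of BMI; both conditions v one) | Power, planned | Power, extended |
|---|---|---|
| 1 and 1 | 91.9% | 92.0% |
| 1.25 and 1.3 | 91.2% | 91.1% |
| 1.5 and 1.5 | 91.5% | 92.0% |
| 2 and 2 | 91.7% | 94.3% |

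Under no treatment effect, the rejection rate was 4.2-4.9% for the planned model and 4.2-4.8% for the extended one.

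**3. The same gain as effective sample size.** Relative efficiency is taken as (mean z extended / mean z planned)², which does not depend on the scale of the odds ratio. Repeating the last three scenarios with 6,000 trials each gives 1.007, 1.029 and 1.095, so about 1-9%. On 2 × 606 = 1,212 participants that is roughly 10 to 110. A further run of 2,000 trials per scenario, with odds ratios of 1.3 to 2.0, gave 1.007 to 1.043.

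**4. Chance imbalance.** The typical BMI difference between arms is √(2/606) = 0.06 SD. At an odds ratio of 1.5 per SD this moves the log odds ratio by 0.057 × ln 1.5 = 0.02. The standard error is √[1/(606·0.05·0.95) + 1/(606·0.10·0.90)] = 0.23. The expected shift is small.

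**5. Can the model carry the terms?** Expected events are 606 × 0.05 + 606 × 0.10 = 91. Coefficients are arm, age, sex, ethnicity, BMI and two for condition, seven in all, or 91 / 7 = 13 events each. If usual care detects only 2.5% in 6 months (assumed: half of 5% a year), events fall to about 76, or 11 each.

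**6. Change of target.** In the strongest scenario the mean estimated log odds ratio moves from 0.76 to 0.85 when the covariates enter. This is the usual non-collapsibility of the odds ratio and is not a correction of bias.

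**The case against.** The strongest reply is that nothing here is an error. The model contains every factor used in the allocation, which is the standard requirement, and further covariates are a matter of choice. That stands.

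A reader might go further and infer that leaving out known risk factors biases the primary comparison or weakens the test. The documents do not support this: allocation is randomised, and the planned model held its type I error in every scenario. Nor can one say that the model adjusts for age, sex and ethnicity alone, since practice is also in it.

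The gain may also be smaller than the evidence review suggests. That section calls these risk factors common and does not say how strongly they predict OSA in this trial's patients. Everyone has BMI of at least 30 and at least one of the two conditions, so much of the contrast is removed by design, and BMI may be up to 3 years out of date. This stands, and it is why the lower end of the range is essentially zero.

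The change is not wholly free either. Baseline assessments list only EQ-5D-5L and the service receipt inventory. The Data sharing plan mentions individual risk factors among the data collected without saying which. Follow-up rules out notes review for intervention participants who test negative and need no further follow-up. That the eligibility values reach the trial database is plausible but not stated.

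Finally, one might argue that the planned imputation is weakened by the same omission. The protocol does not list imputation variables and excludes none. That choice properly belongs in the statistical analysis plan, so it is no part of this point.

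**Conclusion.** The point holds as a minor precision improvement. BMI and qualifying condition are named by the protocol as common risk factors, are required on record for eligibility, and are neither minimised nor adjusted for. Under assumed odds ratios of about 1.25 to 2, adding them gives about 1-9% more effective sample size and roughly 0 to 2.6 points of power, without raising type I error. The upper end needs odds ratios of 2 for both variables; under weak to moderate associations the gain is at most about half a point. These figures rest on assumed associations and an assumed mix of conditions, and the simulations include no practice effect. The validity of the planned model and the figures of 606 and 713 per arm are not in question.

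**What to change.** In the primary model, prespecify two additional fixed effects: BMI as a continuous variable from the GP record used for eligibility, and qualifying condition in three categories (diabetes only, hypertension only, both). Record this before the statisticians are unblinded, and state that the reported odds ratio is conditional on the extended covariate set.

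The cost is one sentence in the plan, three more parameters, and confirmation that the BMI value and qualifying condition are entered in the trial database at eligibility for both arms. No change to the sample size is needed.
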